## Abstract

**Introduction:**

Attempting to curb the rising epidemic of hypertension, South Africa implemented legislation in June 2016 mandating maximum sodium levels in a range of manufactured foods that contribute significantly to population salt intake. This natural experiment, comparing two African countries with and without salt legislation, will provide timely information on the impact of legislative approaches addressing the food supply to improve blood pressure in African populations. This article outlines the design of this ongoing prospective nested cohort study.

**Methods and analysis:**

Baseline sodium intake was assessed in a nested cohort of the WHO Study on global AGEing and adult health (WHO-SAGE) wave 2 (2014–2015), a multinational longitudinal study on the health and well-being of adults and the ageing process. The South African cohort consisted of randomly selected households (n=4030) across the country. Spot and 24-hour urine samples are collected in a random subsample (n=1200) and sodium, potassium, creatinine and iodine analysed. Salt behaviour and sociodemographic data are captured using face-to-face interviews, alongside blood pressure and anthropometric measures. Ghana, the selected control country with no formal salt policy, provided a nested subsample (n=1200) contributing spot and 24-hour urine samples from the SAGE Ghana cohort (n=5000). Follow-up interviews and urine collection (wave 3) in both countries will take place in 2017 (postlegislation) to assess change in population-level sodium intake and blood pressure.

**Ethics and dissemination:**

SAGE was approved by the WHO Ethics Review Committee (reference number RPC149) with local approval from the North-West University Human Research Ethics Committee and University of the Witwatersrand Human Research Ethics Committee (South Africa), and University of Ghana Medical School Ethics and Protocol Review Committee (Ghana). The results of the study will be published in peer-reviewed international journals, presented at national and international conferences, and summarised as research and policy briefs.

Strengths and limitations of this studyRigorous random selection procedure based on a sample designed to be nationally representative.Ongoing data collection within the WHO Study on global AGEing and adult health (WHO-SAGE) cohort to capture salt intake and disease.We were unable to identify the specific foods contributing to salt intake in wave 2.Results may be less representative for the smaller sample of adults aged 18–49 years.Nationwide implementation of salt regulations precludes inclusion of a local control group.

## Current study status

Data collection for wave 2 (baseline for the nested salt substudy) has been completed, while data collection for wave 3 (first follow-up of the nested salt substudy) will take place in 2017 and is estimated to be complete by the end of 2017. Further waves of data collection are planned as part of the multicountry, longitudinal WHO Study on global AGEing and adult health (WHO-SAGE).

## Introduction

Many adults consume more salt daily than is recommended, contributing to the global epidemic of hypertension and cardiovascular disease (CVD).^1^ In low-income and middle-income countries (LMIC), a disproportionately rapid increase in hypertension is occurring without commensurate strategies to halt this growth or mitigate the impact on CVDs and death.^2^ The scale of the problem in South Africa is evident: among six LMICs in one study, South Africa was shown to have the highest prevalence of hypertension (78%) in adults aged 50 years and older.^3^
^4^ Public health strategies are being employed to reduce levels of hypertension, including over 30 countries using legislative changes as part of their salt reduction strategy to meet the WHO and World Health Assembly salt target of 30% reduction in population salt/sodium intake by 2025.^5^
^6^

South African researchers found that non-discretionary salt intake (salt already in processed foods) is estimated to contribute around 60% of the overall daily salt intake, primarily from bread and meat products.^7^ As a result of this research, in March 2013 South Africa was the first country to legislate for mandatory reformulation of a range of foods,^8^ setting maximum sodium levels (mg per 100 g) in targeted processed foods (bread 400 mg; breakfast cereal 500 mg; butter and margarine 550 mg; potato crisps 650 mg; salty snacks 800 mg; raw sausage 800 mg; processed meat 850–950 mg; instant noodle mix 1500 mg; dry soup powder 5500 mg; and stock concentrate 18 000 mg), all identified as contributing significantly to sodium intake in the South African population.^7^
^9^
^10^ The first phase of sodium legislation was implemented in June 2016, with further reductions required in sodium levels across food categories by June 2019.^11^ The legislation is predicted to decrease nationwide salt intake by 0.85 g/day;^12^ reduce annual CVD deaths by 11%; save the government US$51.25 million/year and prevent 2000 cases of poverty annually as a result of saving households more than US$4 million/year in out-of-pocket medical expenses.^13^

A number of collateral issues arise regarding salt intake, such as salt being the main source of iodine fortification, so that successful campaigns to reduce salt intake would have the potential to result in reduced iodine intake.^14^ Another consideration is that dietary sodium-to-potassium ratio may predict CVD mortality better than sodium intake alone.^15^ Additionally, debate continues on the efficacy of legislative versus non-legislative approaches to population salt reduction,^8^
^16^
^17^ including the mechanisms to monitor and enforce such legislation.^18^ From a public health perspective, the major challenge is to evaluate the effects on population health. This paper discusses one effort undertaken to assess a number of health impacts following the sodium legislation in South Africa in comparison to Ghana, an African country with no sodium legislation, through implementation of a large health study in each country.

## Methods and analysis

### Objectives of the research

The primary aim of this study is to evaluate the impact of the sodium legislation on population sodium intake and blood pressure (BP). Secondary objectives are to assess: (1) the relationship between sodium and potassium levels and BP prelegislation and postlegislation; (2) the impact of the sodium legislation on population iodine intake; and (3) the use of spot urine samples as a proxy for 24-hour urine sample collection to measure population salt excretion in a nested biochemical analysis.

### Theory of change

In order to evaluate the impact of policy on the desired outcome, it is critical to appreciate the steps required between policy implementation and change in the outcome. Gertler *et al*^19^ refer to this as the theory of change (how an intervention is supposed to deliver the required results) and propose various models that can be used for this purpose. One of these models, ‘the Results Chain’, has been adapted for our purposes (figure 1) to explore the causal logic underlying the expectation that sodium legislation will impact BP and CVD. The model shows the inputs (legislation and education), activities (food industry formulation changes; also with monitoring of educational/media activities), outputs (change in sodium levels in foods; changes in awareness about dietary salt and hypertension from any educational activities) and outcomes (reduced dietary intake and urinary excretion of salt, reductions in BP, and finally, reductions in CVD mortality, morbidity and associated healthcare spending).

**Figure 1 BMJOPEN2016013316F1:**
[figure not shown]
Results Chain model for the SAGE nested salt substudy. Note: adapted from Gertler *et al*.^19^ *Discretionary and non-discretionary salt use.

Inputs, activities and outputs collectively describe the implementation of the legislation and activities planned by the South African National Department of Health (NDoH) and others. These are the subject of monitoring and process evaluation. The outcomes (results) are the subject of impact evaluation and the main focus of this study. However, the impact evaluation needs to be informed by an assessment of the implementation in order to correctly interpret the results.^19^ For example, without knowing whether the targeted food products comply with the legislation, it would be difficult to attribute change in salt intake to the sodium legislation. As such, a multidisciplinary group including the NDoH will be undertaking these assessments, with contributions from the SAGE collaboration. Gertler *et al*^19^ also suggest that development of the Results Chain model promotes exploration of these assumptions and risks within the proposed causal logic. The assumptions and risks are further explored within the discussion.

### Ghana as a comparison group

Gertler *et al*^19^ also recommend including a comparison group. Ideally, this would be a South African group matched on all characteristics and exposures but not affected by the legislation, with data collected at the same time as those who would be affected by the legislation. However, since the legislation is in force across the whole country, this is not possible. Neighbouring countries such as Lesotho, Swaziland, Botswana, etc, would also not be good candidates for a comparison group as many of the South African food manufacturers export goods to these countries under the South African Development Community (SADC) Regional Free Trade agreement (2008). South Africa is the major source of processed snack food in the SADC region,^20^ providing around 80% of the processed food in Zambia, Namibia and Botswana.^21^ These countries then would most likely be affected by the spillover of the South African sodium legislation. SADC countries form over 80% of South Africa's export market, with exports to the rest of Africa consisting mainly of vehicles and machinery.^22^ As such, Ghana, a non-SADC country and the only other African country to implement WHO-SAGE, was selected as the comparator country. Ghana's adult population is also afflicted by a high prevalence of hypertension (up to 48% of adults generally^23^ and 54% of adults 50+ years of age), increasingly poor risk factor profiles (diet, obesity, physical activity), and poor rates of hypertension awareness and control.^3^ In terms of salt intake, the Ghana Health Service has focused primarily on eradication of iodine deficiency through salt iodisation and education.^24^ At the same time, efforts are underway to boost the salt production industry in Ghana as a method of economic development.^25^
^26^ Salt intakes appear comparable between Ghana and South Africa with studies suggesting that both countries have intakes between 2.3 and 5.5 g sodium/day (equivalent to 5.8–13.8 g salt/day), and higher intakes in urban compared with rural populations.^27^ While there have been some efforts to lower salt intake in community interventions,^28^ until now there appears little evidence to suggest that either mandatory or voluntary sodium targets exist between government and the food industry in Ghana to promote a reduction in population salt intake. However, as in South Africa, it will be critical to monitor activities in Ghana that could influence salt intake between waves 2 and 3 of data collection. There are some risks in taking this pragmatic approach, although local experts will provide ongoing and active assessments in both countries between study waves, and this study team will undertake rigorous comparisons of the nested study groups at waves 2 and 3 to determine the feasibility of this research strategy.

### Study population

#### Random sampling procedure

WHO-SAGE is a multinational study examining the health and well-being of adult populations and the ageing process. Two waves of this longitudinal study have been completed in China, Ghana, India, Mexico, Russia and South Africa.^29^ Further details about WHO-SAGE can be found via the WHO website (http://www.who.int/healthinfo/sage/cohorts/en/) including access to data from SAGE wave 0 (2002–2004), SAGE wave 1 (2007–2010) and SAGE wave 2 (2014/2015) following the completion of data cleaning. SAGE wave 3 will be implemented in 2017, with fund-raising for SAGE wave 4 and beyond ongoing. Evaluation of the health effects of this sodium policy on South African adults, in comparison to Ghanaian adults, is conducted using a nested study design in waves 2 and 3, with monitoring of the nested cohort continuing in subsequent waves of data collection.

In total, 42 464 respondents were recruited across the six countries for wave 1 (2007–2010), including 4223 respondents in South Africa (9% 18–49 years; 40% 50–59 years; 51% 60+ years). Wave 1 respondents were recruited from selected probability sampled enumeration areas (EAs) using a multistage cluster sampling strategy, with stratification by province, residence and race.

The wave 2 sampling strategy was designed to account for expected attrition as a result of participants having moved house or died since wave 1, especially given that over half of the sample were already above 60 years of age in 2007. All wave 1 households were visited for wave 2 data collection (including a verbal autopsy for those participants no longer alive). Replacements for sample attrition used a systematic sampling approach to randomly select new households using EA aerial photographic maps on which dwellings are clearly visible, starting at a random point on the periphery of the EA and following predetermined routes. Households were then classified into the following mutually exclusive categories: (1) SAGE wave 1 follow-up households with one or more members aged 50 years or older targeted for selection; (2) new households with one or more members aged 50 years or older; (3) SAGE wave 1 follow-up households which include residents aged 18–49 targeted for selection or (4) new households which include residents aged 18–49. Younger adults are allowed to ‘age-in’ to the older adult group, with targeted refreshing of the youngest ages (18–23) in the younger adult sample.

The sampling method used in SAGE Ghana wave 2 followed a similar design, based on the 2003 World Health Survey/SAGE wave 0^30^ with primary sampling units (PSUs) stratified by region and location (urban/rural). Selection of the PSUs was based on proportional allocation by size using the same follow-up and random systematic sampling method as South Africa.

### Selection and data collection in the nested cohort

Both South Africa and Ghana include between 3500 to 4500 households for SAGE's main survey sample. The samples selected for urine collection (n=1200 in each country) from waves 2 and 3 of the main study are of adults aged 18+ years, with the final distribution in the main and nested studies reflecting the weighting towards recruiting more adults aged 50+ years. In South Africa, the nested study respondents were sampled from among the first wave 2 households visited within each probability sampled EA (day 1 in the EA). This approach was taken to prioritise the shipment of all collected urine samples to a central laboratory (Global Clinical and Viral Laboratory, Durban) within 3 days of collection while maintaining a cold chain regardless of where urine collection took place. This was necessary as there were no decentralised facilities available to freeze urine. The SAGE South Africa team used 20 survey teams (one nurse and three interviewers per team) simultaneously collecting data and urine/blood samples from respondents across all provinces in the country over a 5-month period (August to December 2015).

Selection of the nested study sample in Ghana differed slightly from the one in South Africa. All urine samples were collected by just four fieldwork teams (one research assistant and four interviewers per team) moving region to region over a 10-month period (September 2014 to June 2015). To facilitate this approach, EAs were randomly selected, with stratification by urban/rural, from the three geographical areas (savannah, forest and coastal) of Ghana and designated ‘urine EAs’ from which the target 1200 respondents were recruited.

Inclusion criteria for urine collection were: respondent must be part of the WHO-SAGE cohort, with no indication of urinary incontinence or other condition that could impede 24-hour urine collection; and if female, not menstruating, pregnant or breast feeding on the day of collection. All respondents who provided samples in wave 2 will be approached again in wave 3 in both countries, with procedures as described earlier for replacement and refreshment of the sample.

### Study measures included in WHO-SAGE

All survey teams are trained with support from WHO Geneva, with survey teams using standardised household, individual and proxy questionnaires, anthropometry, blood sampling, BP and physical function tests as described previously in SAGE wave 1.^29^ Study measures are listed in table 1 and translation and back-translation protocols are in place for the survey instruments. Interviewers speak the respondents' home languages with consent forms available in the most widely spoken languages for each area.

**Table 1 BMJOPEN2016013316TB1:** Primary and secondary outcome measures

Variable	Primary/secondary outcome	Method of measurement
Sodium intake	Primary	24-hour urinary sodium excretion
Blood pressure	Primary	Validated, automated wrist BP monitor—triplicate measure
Potassium intake	Secondary	24-hour urinary potassium excretion
Iodine status	Secondary	Urine iodine concentration
Cigarette smoke exposure	Secondary	Urine cotinine concentration and questionnaire
Medication use	Secondary	Questionnaire
Dietary salt behaviour	Secondary	Questionnaire*
Alcohol consumption	Secondary	Questionnaire
Physical activity	Secondary	Global Physical Activity Questionnaire^44^
Body composition	Secondary	Height, weight, waist and hip circumference
Quality of life	Secondary	WHO Quality of Life instrument (WHOQoL)^45^

*The dietary salt questionnaire consists of the following questions: (1) Do you add salt to food at the table? (Always, rarely, sometimes, often, never); (2) In the food you eat at home, salt is added in cooking [always, rarely, sometimes, often, never); (3) How much salt do you think you consume? (Far too much, too much, just the right amount, too little, far too little, don't know, refused); (4) Do you think a high salt diet could cause a serious health problem? (Yes, no, don't know, refused); (5) Do you do anything on a regular basis to control your salt or sodium intake? (Yes, no, don't know, refused).

BP, blood pressure; WHOQoL, WHO Quality of Life instrument.

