### Urine collection in the nested study (waves 2 and 3)

The study protocol used for sodium determination in 24-hour urine samples followed the WHO/Pan American Health Organization (PAHO) guidelines.^31^ Respondents were requested to collect all urine produced for 24 hours, excluding the first pass urine on day 1, but including the first urine of the following morning (day 2) in a 5 L plastic container using 1 g thymol as preservative. The spot sample was collected without preservative from the second urine passed on day 1 (marking the start of the 24-hour collection) and decanted into three 15 mL Porvair tubes (Porvair Sciences, Leatherhead, UK), then kept in a thermoelectric cooler box powered by the fieldwork vehicles and containing ice packs to maintain a lowered temperature. The 24-hour sample was collected the next morning, total volumes were recorded and aliquots (4×15 mL Porvair tubes) generated with all samples then shipped to the laboratory maintaining the cold chain using precooled ice packs as a means to maintain temperature control. When the samples arrived at the laboratory, the cooler box was examined and the temperature of the samples noted and recorded.

Owing to differences in available resources, duration of data collection and logistical challenges presented by each country, Ghana and South Africa used different methods of urine preservation in wave 2. In Ghana, the survey team kept urine samples in hospitals, clinics and health centres with laboratory facilities in the EA in which they were working. Samples were taken on ice to the central university laboratory between the first and fifth days of interviews in each EA. This was necessary as there were limited options and resources for commercial transport of samples within Ghana. Additionally, with Ghana's tropical climate and a smaller fieldwork team than in South Africa, the possibility that samples may stand for longer in a warmer climate prior to collection necessitated the use of 37% hydrochloric acid (HCl; AnalaR NORMAPUR) as a preservative added to both the 24-hour (10 mL per 5 L collection container) and spot urine (10 mL per 2 L collection container) samples.

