In South Africa, thymol preservative, a crystalline natural derivative of the thyme plant, is used as it is easier and safer to transport and handle than commonly used liquid acids by the 20 operating fieldwork teams and courier companies, many of which will not transport liquid acids. In both countries, survey teams explain the dangers of the preservatives to respondents, and are trained in handling the preservatives and biological materials. Both thymol and HCl have been shown to prevent changes in urinary creatinine, sodium and potassium concentrations for up to 5 days.^32^

Incomplete 24-hour urine collections are assumed if: total volume ≤300 mL; or creatinine excretion ≤4 mmol/day (women) or ≤6 mmol/day (men).^33^ The use of para-amino benzoic acid (PABA) has been suggested as a more accurate method than creatinine to validate 24-hour urine collection completeness.^34^ However, PABA recovery rate declines with age in respondents older than 30 years.^35^ Considering this together with the increased risk for non-compliance and attrition due to the additional burden of remembering to take the PABA pill 3 days before the urine collection, as discussed in the WHO/PAHO guidelines for sodium determination in 24-hour urine samples,^31^ PABA is not used in this study.

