### Urine analysis

Sodium and potassium were determined using the indirect ion-selective electrode method and creatinine analysed using the standardised urinary Jaffe kinetic method (South Africa: Beckman Coulter Synchron DXC600/800 System; Ghana: BioSystems Analyzer A25). The WHO population target for salt intake is 5 g salt (NaCl) per day, equivalent to urinary sodium excretion 85 mmol/24 hour. Urinary potassium should be >70 mmol/24 hour, with a sodium-to-potassium ratio <1 shown to be protective for all-cause, cardiovascular and ischaemic heart disease mortality.^15^ With the exception of iodine, all South African samples were analysed at a single laboratory in Durban (Global Clinical and Viral Laboratory). In Ghana, with the exception of iodine, all samples were analysed at a single laboratory in Accra (University of Ghana Chemical Pathology Laboratory in the School of Allied Health Sciences).

Urine samples for iodine analysis from both countries were stored at −20° C and batch analysed using the Sandell-Kolthoff method with ammonium persulfate digestion and microplate reading^36^ at the North-West University Centre of Excellence for Nutrition. The laboratory participates successfully in the Program to Ensure the Quality of Urinary Iodine Procedures (EQUIP, US Centres for Disease Control and Prevention, Atlanta, Georgia, USA).^37^ A median of <100 μg iodine/L indicates population-level deficiency (there is no reference range for individuals).^38^

Even though there is no evidence that the addition of preserving substances such as HCl and thymol affects urinary iodine concentrations,^39^ we undertook testing to examine the influence of adding thymol or HCl to urine samples (n=20) on urinary iodine concentrations. The results indicated no significant or relevant (below assay coefficient of variation) differences when compared with samples without added preservatives (results not shown here).

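### Objective 2 asks about iodine intake, but the only iodine measure named is a concentration, which also moves with urine volume; 24-hour excretion should be named beside it

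*Protocol article*

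**What the plan says.** Under Objectives of the research, the second secondary objective of the protocol article is to assess "the impact of the sodium legislation on population iodine intake".

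Table 1 (Study measures included in WHO-SAGE) has a row for sodium intake, measured by "24-hour urinary sodium excretion", and a row for potassium intake, measured by "24-hour urinary potassium excretion". The iodine row is labelled as status, not intake, and its method is "Urine iodine concentration".

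For the 24-hour sample, the urine collection section says that "total volumes were recorded". The same section gives the completeness rule: "Incomplete 24-hour urine collections are assumed if: total volume ≤300 mL", or creatinine excretion at or below 4 mmol/day in women or 6 mmol/day in men.

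Urine analysis gives one rule for reading iodine: a median below 100 µg/L marks deficiency in a population. The section on comparing spot and 24-hour urine mentions 24-hour iodine excretion, but only as the reference for testing spot-urine equations, which is objective 3. The article does not say whether the concentration in Table 1 comes from the spot or the 24-hour sample.

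**The concern.** The objective and the named measure are on different scales. A change in concentration between waves mixes a change in iodine excreted with a change in urine volume. For sodium and potassium the article removes volume by using excretion; for iodine it does not, although the same volumes are available.

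The iodine objective is there to catch an unwanted effect. The Introduction notes that salt carries the iodine fortification, so that less salt could mean less iodine, and the Discussion wants surveillance to guide the iodine level in salt. A volume change could conceal a real fall in intake or suggest one that did not happen.

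The calendar does not rule this out. Wave 2 collection ran from August to December 2015 in South Africa and from September 2014 to June 2015 in Ghana. Wave 3 is placed only in 2017. Season and climate may therefore differ between waves, and not equally in the two countries.

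**Working it through.** **The plan's own figure.** The article gives no iodine calculation. Its one sample-size figure, for salt, uses a difference of 0.85 g/day and a variance of 35 (Data capture, analysis and statistical power). With two independent means, two-sided 5% and 80% power:

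n = 2 × 35 × (1.960 + 0.842)² / 0.85² = 760.4, so 761 per group.

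This reproduces the stated 761. The point below does not affect it.

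**Scale of the effect.** The same section gives a baseline salt intake of 8.1 g/day, so the modelled relative fall is 0.85/8.1 = 10.5%. The share of this that carries over to iodine is not in the document. Taking 25% to 100% as an assumed range, the iodine fall is 2.6% to 10.5%.

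**What concentration shows.** Let e be the relative change in excretion and v the relative change in volume. Then

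change in concentration = (1 + e)/(1 + v) − 1.

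| Volume change | Concentration change, intake unchanged | Concentration change, intake down 10.5% |
|---|---|---|
| −10.5% | +11.7% | 0.0% |
| −10% | +11.1% | −0.5% |
| −5% | +5.3% | −5.8% |
| 0 | 0.0% | −10.5% |
| +5% | −4.8% | −14.8% |
| +10% | −9.1% | −18.6% |

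- To hide the fall completely, set v = e: a volume fall of 2.6% to 10.5%.
- To mimic it with intake unchanged, set v = 1/(1 + e) − 1 with e negative: a volume rise of 2.7% (1/0.974) to 11.7% (1/0.895).

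**Comparison with Ghana.** On the ratio scale the between-country contrast is [(1 + e_SA)/(1 + e_GH)] / [(1 + v_SA)/(1 + v_GH)]. Only the relative volume shift matters. If volume rises 10% in both countries and intake falls 10.5% in South Africa alone, the contrast is (0.895/1.10)/(1/1.10) = 0.895, which is the correct −10.5%. The percentages above therefore apply to a shift in South Africa relative to Ghana.

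**Status cut-off.** At an assumed excretion of 150 µg/day, concentration is 150/1.4 = 107 µg/L at 1.4 L and 150/1.6 = 94 µg/L at 1.6 L. The same excretion falls on either side of 100 µg/L.

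**What excretion shows.** Concentration times total volume cancels v, so a 10.5% fall reads as −10.5% at any urine volume, provided that the collection is complete. If only a fraction f of the day's urine is collected, measured excretion is f times the true value, while concentration stays about the same if the lost urine is similar to the rest. A relative fall of 10.5% in f would thus mimic the effect on the excretion scale. The two measures fail in different ways.

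**The case against.** The strongest reply is that the table is consistent in itself. Its iodine row is labelled as status, concentration is the scale on which the 100 µg/L criterion is defined, and the Discussion speaks of monitoring iodine status. On this reading the loose word is intake, in objective 2. This stands as far as status goes: concentration is right for that purpose and should stay. It does not supply a measure for the objective as written.

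A second reply is that 24-hour iodine excretion will exist anyway, because the spot comparison needs it, and that an analysis plan may assign it to objective 2. The article promises such a plan. But it does name an outcome measure for iodine, and that measure does not match the stated objective. The existence of the data makes correction cheap; it does not remove the mismatch.

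A third reply is that excretion has its own bias. This stands. The completeness rule is a low floor: at an assumed 1.5 L/day, the 300 mL limit alone rejects only collections that have lost 80% of the urine (300/1500 = 20% kept), and moderate losses may also pass the creatinine limits. The article expects incomplete samples when it raises 761 to 1200.

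Two stronger arguments are tempting but not supported:

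- *Excretion is more precise.* With an assumed log-SD of excretion of 0.6, a volume CV of 30% to 60% and independence, log concentration has (0.36 + 0.086)/0.36 = 1.24 to (0.36 + 0.307)/0.36 = 1.85 times the variance of log excretion. With correlation ρ between log excretion and log volume, the order reverses once ρ exceeds s/(2 × 0.6), where s is the log-SD of volume (0.29 to 0.55): that is, above about 0.24 to 0.46. Under-collection by itself pushes ρ upwards. The article gives none of these quantities.
- *Acid in Ghana's spot samples dilutes iodine.* This matters only if spot samples supply the concentration, which the article does not say. In a 1.5 L 24-hour sample the dilution is 10/1510 = 0.7%, and a similar dilution in both waves would largely cancel in the change within Ghana.

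**Conclusion.** The point holds as a mismatch between objective 2 and its only named measure. A change in volume between waves that differs between the countries by about the size of the modelled salt fall (10.5%, or 2.6% if only a quarter carries over to iodine) could hide or mimic a change in iodine intake.

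A reader might infer that the iodine conclusion will be wrong. The document does not support that: it reports no volume shift, and a common shift cancels against Ghana. Nor is 10.5% an upper limit on the iodine fall, since education also targets discretionary salt; it is only a scale. A reader might also infer that concentration should be replaced. It should not, because it remains the right scale for status and is less exposed to incomplete collection.

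The result rests on the assumed proportionality of iodine to salt and on the identity that concentration is excretion divided by volume. The outcome is secondary, the sodium and blood pressure results are unaffected, and the change is a worthwhile improvement rather than a condition for the study.

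**What to change.** In Table 1, or where the analysis of objective 2 is set out:

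1. Name 24-hour urinary iodine excretion (iodine concentration in the 24-hour aliquot times recorded total volume, complete collections only) as the measure of change in intake, compared by country and wave on the log scale or as medians.
2. Keep the median concentration against 100 µg/L as the status criterion, and state that it comes from the same 24-hour aliquot.
3. Report both for each country and wave. If they disagree, say so, and consider volume shift and under-collection as explanations.

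The cost is a line or two of text and one multiplication. Volumes are already recorded, and the planned spot comparison already needs iodine measured in the 24-hour sample. The small downside is that excretion inherits under-collection that passes the completeness rule, which is why concentration is reported beside it.
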